## 8.2 Expectedness

The expectedness of an adverse reaction is set out in the Reference Safety Information (RSI). Only those SAR which are listed in the RSI may be considered 'expected'. In determining whether an adverse event is unexpected, consideration shall be given to whether the event adds significant information on the specificity, increase of occurrence, or severity of a known, already documented serious adverse reaction. Specific examples would be (a) acute renal failure as an expected

|                                                                    |                                              |                                |
|--------------------------------------------------------------------|----------------------------------------------|--------------------------------|
| Clinical Trial Code: PROTECT
EU trial number: 2022-502332-39-00 | Trial Protocol
(Version 06; (01.10.2024)) | Page 85 of 110
CONFIDENTIAL |
|--------------------------------------------------------------------|----------------------------------------------|--------------------------------|

adverse reaction with a subsequent new occurrence of interstitial nephritis and (b) hepatitis with a first occurrence of fulminant hepatitis.

In this trial Additional Information on Sirolimus including Reference Safety Information will be used as RSI. Each serious adverse reaction (SAR) is to be classified as unexpected.

### 8.3 Suspected Unexpected Serious Adverse Reaction (SUSAR)

SAEs that are both 'suspected', i.e., potentially related to the investigational medicinal products (IMPs) and 'unexpected' (for definition see above) are to be classified as Suspected Unexpected Serious Adverse Reactions (SUSARs).

In case, either the investigator who initially reported the SAE or the Sponsor's designated person(s) (second assessor(s)), classifies the SAE as potentially related to the IMPs and the SAE is 'unexpected' it will be categorized as a SUSAR.

All SUSARs are subject to an expedited reporting (see section 8.8).

### 8.4 Characteristics of Adverse Events

#### 8.4.1 Grading of AEs

The grading of AEs in this clinical trial will be carried out based on the 5-grade scale defined in the CTCAE V 5.0:

|          |                                                                                                                                                                          |
|----------|--------------------------------------------------------------------------------------------------------------------------------------------------------------------------|
| Grade 1: | Mild; asymptomatic or mild symptoms; clinical or diagnostic observations only; intervention not indicated.                                                               |
| Grade 2: | Moderate; minimal, local or non-invasive intervention indicated; limiting age-appropriate instrumental ADL*.                                                             |
| Grade 3: | Severe or medically significant but not immediately life-threatening; hospitalization or prolongation of hospitalization indicated; disabling; limiting self-care ADL**. |
| Grade 4: | Life threatening consequences; urgent intervention indicated.                                                                                                            |
| Grade 5: | Death related to AE.                                                                                                                                                     |

Activities of Daily Living (ADL)

\*Instrumental ADL refer to preparing meals, shopping for groceries or clothes, using the telephone, managing money, etc.

\*\*Self-care ADL refer to bathing, dressing and undressing, feeding self, using the toilet, taking medications, and not bedridden.

The grading of all AEs listed in the CTCAE v 5.0 will be based on the information contained therein. The grading of all other AEs, i.e., those which are not listed in the CTCAE v 5.0 will be performed by a responsible investigator, based on definitions given above.

If an AE shows an undulating course of intensity, it must be documented only once with predominant or medically most appropriate intensity.

Clarification of the difference in meaning between "serious" and "severe": The terms "serious" and "severe" are not synonymous. The term "severe" should be used to describe the intensity (severity) of a specific event; the event itself, however, may be of relatively minor significance (such as severe headache). This is not the same as "serious", which is based on the existence of at least one of the above-mentioned seriousness criteria.

|                                                                    |                                              |                                |
|--------------------------------------------------------------------|----------------------------------------------|--------------------------------|
| Clinical Trial Code: PROTECT
EU trial number: 2022-502332-39-00 | Trial Protocol
(Version 06; (01.10.2024)) | Page 86 of 110
CONFIDENTIAL |
|--------------------------------------------------------------------|----------------------------------------------|--------------------------------|

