| Grade 4 thrombocytopenia                                                                                                                                              | Interrupt study drug until recovery to $\leq$ grade 1. Then reduce subsequent doses to 50%.                                                                                                                                                                                                                                                                                                                           |
| Grade 2 neutropenia or anaemia                                                                                                                                        | No action                                                                                                                                                                                                                                                                                                                                                                                                             |
| Grade 3 neutropenia or anaemia                                                                                                                                        | Interrupt study drug until resolution to $\leq$ grade 1 or screening level. If resolution occurs $\leq 7$ days, reintroduce study drug at the dose level prior to interruption. If resolution occurs $> 7$ days, or event reoccurs within 28 days, reduce subsequent doses to 50%.                                                                                                                                    |
| Grade 4 neutropenia or anaemia                                                                                                                                        | Interrupt study drug until recovery to $\leq$ grade 1. Then reduce subsequent doses to 50%.                                                                                                                                                                                                                                                                                                                           |

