### 7.1 Temporary Discontinuation from Treatment with the IMP

Temporary treatment (IMP) discontinuation at the discretion of the investigator is defined as one or more doses not administered to the subject.

Temporary treatment discontinuation may be considered by the investigator because of the following:

- Sirolimus may affect the response to vaccination. Sirolimus should be paused 2 weeks before until 2 weeks after receiving a live vaccine. The SmPC of Sirolimus recommends avoiding live vaccines during treatment with Sirolimus. Individual risks/ benefits should be discussed with infectious disease specialists.
- Surgical interventions: Treatment with sirolimus may affect wound healing. We recommend pausing treatment 14 days before until 14 days after elective surgical interventions. For non-elective interventions, therapy should also be paused until 14 days after the procedure.
- For a single grade 3 adverse event or for less serious adverse events, e.g. uncomplicated (viral) infections, sirolimus can be temporarily discontinued at the discretion of the investigator (for details see chapter 5.5.3)
- Grade 4 adverse event (for details see chapter 5.5.3)

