### 7.2 Permanent Discontinuation from Treatment with the IMP

Permanent treatment discontinuation with the IMP is any treatment discontinuation associated with the investigator's or the legal guardian(s) of the subject's definitive decision not to re-expose the subject to the IMP. The following criteria will lead to a permanent treatment discontinuation:

- Withdrawal of consent to trial participation
- Loss to follow-up
- Death
- Legal guardian(s)'s request, i.e. withdrawal of consent for treatment → documentation in source data
- Use of illicit drugs, prohibited concomitant medications (e.g. other mTOR inhibitors), or other substances that, in the opinion of the investigator, are likely to increase toxicity or otherwise confound the results while taking the IMP.
- Recurring grade 4 adverse events (AE) or serious and unexpected adverse events (SAE) related to the IMP require permanent discontinuation of sirolimus.

|                                                                    |                                              |                                |
|--------------------------------------------------------------------|----------------------------------------------|--------------------------------|
| Clinical Trial Code: PROTECT
EU trial number: 2022-502332-39-00 | Trial Protocol
(Version 06; (01.10.2024)) | Page 81 of 110
CONFIDENTIAL |
|--------------------------------------------------------------------|----------------------------------------------|--------------------------------|

- Lack of compliance, e.g. caregivers and participants fail to attend interim visits or to perform self-medication according to schedule.
- Any additional diagnosis due to which, in the investigator's opinion, participation in the treatment group of the trial may pose a risk for the study participant or that may interfere with protocol adherence.
- Negative Risk-Benefit Evaluation
- Subject did not meet in-/exclusion criteria (coming to light after inclusion), if it poses a risk for the study participant to continue the IMP in the opinion of the investigator.

The reason for the permanent discontinuation of treatment with IMP has to be documented in the source data.

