## 8.6 Period of Observation and Documentation

### 8.6.1 Adverse Events (AEs)

**AEs** will be ascertained by the investigators using non-leading questions, noted as spontaneously reported by the caregiver(s) of the subjects to the medical staff at any time during the trial or observed at any of the clinical trial visit.

The observational period begins with the signature of the informed consent form (ICF) and ends with the end of trial visit (V13). Same applies for SAEs/AESIs. AEs will be interrogated for at each contact between the responsible investigator and the caregiver(s) of the clinical trial subject. Thereafter, the investigator does not need to actively monitor subjects for adverse events. However, if the investigator becomes aware of a serious adverse event with a suspected causal relationship to the IMP (SAR) that occurred after the end of the observational period he or she shall report the SAE without undue delay to the Sponsor, as long as the clinical trial is still ongoing. This kind of SARs is also to be documented in the eCRF.

AEs will be documented in the subject file and in the eCRF. AEs will be reported with patient number, start and end date, description, grading, seriousness, relationship, action taken and outcome. These are the parameters that can be found on the standard AE-eCRF page. If applicable, all medical diagnoses or symptoms occurring prior to the beginning of the period of observation and documentation will be recorded in the eCRF as medical history.

The following general rules apply to the documentation of the AEs and SAEs: The start date of a SAE must not be earlier than that of the corresponding AE. The end date of a SAE is typically the same as that of the AE. The end date of the SAE must not be later than the end date of the corresponding AE. AEs and SAEs that are ongoing at the time of death are considered not resolved or resolving.

All SAEs/AESIs and their relevance for the benefit-risk assessment of the clinical trial will be evaluated continuously during the clinical trial and for the final report. All SAEs/AESIs will be documented in the eCRF and in the 'SAE/AESI Report Form' (see section 8.7.1).

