## 9.5 Secondary Analyses

### 9.5.1 Main Trial Analyses

**All secondary parameters** will be analyzed for the FAS.

BSID-III cognitive scale at the age of 1 year will be analysed similar to the primary endpoint. In addition, the BSID-III cognitive scale and important subscales will be analysed descriptively by group and time point using standard descriptive measures for continuous variables. The VABS total scales, important VABS subscales, ADOS total scales, and important ADOS subscales will be analysed descriptively by group and time point using standard descriptive measures for continuous variables, as well. In addition, for cognitive impairment and autism spectrum disorders at 1 and 2 years of age, 95% CIs will be calculated by treatment group in addition to the relative frequencies using the method of Wilson. The M-CHAT-R/F and TAND will be analysed descriptively by group and time point using absolute and relative frequencies.

The MRI characteristics (as defined in Section 6.8) will be analysed by group and time point, i.e. randomization (last image before randomization) and at 2 years of age  $\pm$  6 months.

Seizure characteristics, EEG characteristics, abdominal sonography characteristics, ECG and echocardiography characteristics (as defined in Section 6.8) will be analysed by treatment group and time point (if applicable).

All **safety parameters** will be analyzed for the SAF. Only treatment emergent-event adverse events will be analysed. Frequencies (number of adverse events & number and percentage of patients with at least one adverse event) will be tabulated according to system organ class and preferred term. One table each will be created showing: all adverse events, all serious adverse events, all adverse events of special interest, all non-serious adverse events, all adverse events leading to death, all adverse events related to the treatment (treated group only), all adverse events by severity. In addition, adverse events and special situations will be analysed by categories defined in the eCRF (number of events & number and percentage of patients with at least one event).

For laboratory values and vital signs, the analyses will be conducted by visit and shift tables comparing all values by visit to the relevant baseline value will be displayed additionally.

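### An undulating adverse event is recorded once at a discretionary grade, so a short grade 3–4 phase can be missing from the table of adverse events by severity

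*Protocol*

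**What the plan says.** Section 8.4.1 sets the scale: "The grading of AEs in this clinical trial will be carried out based on the 5-grade scale defined in the CTCAE V 5.0". For an event whose intensity goes up and down, the same section says that "it must be documented only once with predominant or medically most appropriate intensity".

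Section 8.6.1 describes the AE page: "AEs will be reported with patient number, start and end date, description, grading, seriousness, relationship, action taken and outcome". That is one grading per event. A worst-grade field or a dated record of grade changes is not listed.

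Among the safety tables in section 9.5.1 is one of "all adverse events by severity".

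Other sections act on the grade that an event reaches. Table 6 in section 5.5.3 has separate rows by grade, for example "Grade 4 neutropenia or anaemia". Section 7.1 opens one of its reasons for a temporary stop with "For a single grade 3 adverse event or for less serious adverse events". Section 7.2 makes recurrence of grade 4 events one of the criteria for permanent discontinuation. Under section 5.1.2, trial personnel at the sites are not blinded.

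**The concern.** A safety table by severity is normally read as showing the worst that each child experienced. Under section 8.4.1 it need not. The investigator may enter the grade that prevailed for most of the event, or the grade judged most fitting. Neither term is defined, and the choice is made with the treatment known.

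Two things are at stake. First, the severity table can understate how many children had a severe phase. The comparison is small: with 30 children planned per arm, one child is 1/30, or 3.3 percentage points. Second, the recorded grade may not match the grade that led to an interruption, a dose reduction or a stop, which makes the safety data harder to reconcile.

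This is a rule about what is collected. If the peak grade is not entered on the AE page, a statistical analysis plan cannot restore it from the AE data. The matter therefore belongs in the protocol, although the SAP is not at hand.

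**Working it through.** The protocol states no figure on this point, so the check sets its provisions side by side.

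**Step 1: what one record can show.** Take an assumed example: an undulating AE at grade 2 on 20 days in all and at grade 3 on 2 days, so the peak fills 2/22 = 9% of the course.
- Predominant intensity: grade 2. The grade 3 phase is not in the AE record.
- Medically most appropriate intensity: grade 2 or grade 3, as the investigator judges.
- Highest grade reached: grade 3.

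The rule therefore allows the peak to be lost but does not force it. With a single grading per event (8.6.1), whatever is entered is all that the severity table can use.

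**Step 2: is the highest grade required elsewhere?** Sections 8.1 to 8.6, 5.5.3, 7.1, 7.2 and 9.5.1 contain no such requirement, and none asks for a new record when the grade rises.

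**Step 3: recorded grade against triggering grade.** In Table 6, non-infectious pneumonitis of grade 2 and of grade 3 have different rows. A child handled under the grade 3 row could have the event recorded as grade 2. For mucositis, Table 6 puts intolerable grade 2 and grade 3 in one row, so the mismatch there concerns the severity table and section 7.1 more than Table 6.

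**Step 4: recurrence.** Several Table 6 rows allow the drug to be restarted once the event has fallen to grade 1 or below, and then ask whether it recurs within 28 days. An event that settles at grade 1 and rises again could be read as one undulating AE with one record, or as a recurrence. Section 8.1.1 lists recurrence of disease, and more frequent or more intense episodic disease, among possible AEs, but does not say where one record ends and the next begins.

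**Step 5: what is kept by another route.**
- Serious AEs and AEs of special interest have their own tables (9.5.1), whatever AE grade is entered. Grade 4 is described as life-threatening (8.4.1), which overlaps a seriousness criterion in 8.1.2, and 8.1.2 names blood dyscrasias among events usually to be considered serious.
- Laboratory values are entered in the eCRF (6.8) and analysed by visit, and "shift tables comparing all values by visit to the relevant baseline value will be displayed additionally".
- Dose changes and the length of interruptions are recorded separately (5.4, 5.5.3, 6.8).

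What remains exposed is mainly a non-serious grade 3 phase of an event that is not a laboratory finding, together with laboratory peaks that fall between visits. Section 8.4.1 itself stresses that severe and serious are different things, so a non-serious grade 3 phase has no second table to appear in.

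**The case against.** The strongest reply is that the rule offers two options and that the second permits the peak grade. That stands: the severe phase can go missing, but nothing says that it will. It is also right that the sentence covers only an undulating course. A single rise and fall after the drug is interrupted is not clearly within it.

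Four stronger readings are tempting, and the documents do not support them.

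- *A reader might infer that any peak lasting less than half the event is down-graded.* That would follow only if predominant intensity were the sole option.
- *A reader might take brief grade 4 neutropenia as the typical loss.* It is among the better protected events: such a peak would usually be reported as serious, and a value seen at a visit stays in the shift tables.
- *A reader might infer that the DSMB and the risk-benefit evaluations see too few severe events.* No section says that either sees only the AE grade. The evaluators are subinvestigators at the child's own site (1.3.10, 6.5), and the DSMB charter is a separate document not at hand.
- *A reader might put a number on it.* Neutropenia occurred in 21% to 42% of children under 2 years in the protocol's Table 2. If 10% to 20% of those peaked at grade 3–4, then 30 × 0.21 × 0.10 = 0.6 to 30 × 0.42 × 0.20 = 2.5 treated infants. The 10% to 20% is an assumption without a source in the protocol. The calculation also needs every such peak to be down-graded, which the second option contradicts, and it uses a laboratory event. Section 1.3.7.1 reports mostly grade 1 and 2 events, and none of grade 4 or higher, in that cohort.

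On direction, the rule is the same in both arms. Table 1 schedules haematology and chemistry at up to 12 visits after the start (V2 to V13) on sirolimus and at 3 (V6, V8, V12) in controls. Fluctuation in laboratory values will be seen more often on sirolimus, but so will the peaks. Different use of the discretion between arms is possible in an open-label trial; it is not shown.

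**Conclusion.** The point holds in a limited form. Section 8.4.1 fixes a recording rule that does not require the highest grade. At the unblinded investigator's discretion, a short grade 3–4 phase of an undulating AE can therefore be absent from the severity table, and the recorded grade can differ from the grade acted on under 5.5.3, 7.1 or 7.2. The exposure is mainly non-serious, non-laboratory grade 3 phases, mucositis being an example.

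The number affected cannot be derived from the documents, so no estimate is given. The conclusion rests on the AE page carrying only the fields listed in 8.6.1. If the eCRF also captures a worst grade or dated grade changes, the point reduces to reconciling the wording. The primary endpoint is not touched. The change is worth making because it is cheap and because the loss cannot be repaired from the AE record at the analysis stage.

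**What to change.** In section 8.4.1 and the eCRF completion guideline, replace the sentence on undulating events with a rule that such an event is documented once with the highest CTCAE grade reached. Specify the severity table by maximum grade per patient.

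State when a renewed rise in grade after improvement is a new AE record and when it continues the old one. Reconcile this with the recurrence wording in sections 5.5.3 and 7.2, so that a recurrence recognised for the dosing rules can also be found in the AE data. This concerns recording only: no grade threshold and no rule on interruption, dose or discontinuation needs to change.

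The cost is one replaced sentence, a short clarification on new records and an update of the guideline. The downside is that entries already made for fluctuating AEs need a query to obtain the highest grade, and some sites may have to return to source records.
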